#### 15.3.3 Missing value processing method

In the analysis of validation variables, LOCF (Last Observed Carried Forward) method is applied to replace missing values, and safety evaluation parameters are analyzed without substitution if there is a mistake.

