### 9.3 Sample size

#### 9.3.1 Sample size

##### - Total 200 patients (PGA Group 100 patients, Placebo Group 100patients)

Based on published literature, we assumed that 31% of the cases of CIN 1 would resolve spontaneously, and a clinically significant difference was estimated at 20%. 80 patients per group.

| Group | Dose | Patient | Expected response Rate | Expected response patient | Duration of treatment/Observation |
| --- | --- | --- | --- | --- | --- |
| Placebo | - | 80 | 31% | 24.8 | administered once daily for 4 weeks /  observation for 8 weeks |
| PGA | 1,500mg/day | 80 | 51% | 40.8 |  |
| Total | - | 160 |  |  |  |

Cervical intraepithelial neoplasia (CIN I) can act as a precursor to invasive cervical cancer and is the most common significant gynecologic disease in women of reproductive age. study, we investigated clinical efficacy and immune response of oral administration of γ-PGA from women with cervical intraepithelial neoplasia 1 (CIN 1) in phase 2b study

H_0_ : p_1_≦p2 vs. H_1_ : p_1_>p_2_

p_1_ : Response rate of treatment, p_2_: Response rate of Control

Expected response rate: PGA Group: 81%, Control Group: 51%

significance level : 0.05, statistical power : 80%, one-sided test

The Sample size is total 160 patients, 80 patients per group when the Single stage method.

If 20% drop out is considered, the sample is total 200 patients, 100 patients per group

The sample size is according to the Two stage optimal design (Jung(2008)) Method is shown in the following table.

[Jung(2008) Two-stage]

| Stage | Patient | Difference between two groups (Treatment patient-Control patient) | 제 significance level, statistical power |
| --- | --- | --- | --- |
| 1  2 | 43  80(43+37) | +2  +11 | 0.461, 0.800 |

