###### Prohibited drugs

The drugs to be prohibited during the clinical trial period are as follows. When the use of medication for concomitant medication is required, the clinical trial subject should stop the clinical trial

1) Steroids: Betametasone, Dexametasone, Prednisolone, Hydrocortisone, etc., except hen except when applied locally to skin or eyes.

2) Immunomodulators: growth hormone, EPO (Erythropoietine), albumin preparations, transfusion of whole blood and leukocyte components, etc

3) Others: Supplements and vitamin preparations other than clinical trial drugs. Chinese medicine

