**[14] Clinical Trial Suspension / Dropout Criteria and Analysis Exclusion Criteria**

### 14.1 Clinical Trial suspension ·dropout criteria

The followings are the items which can be the clinical trial stoppage and dropout of the clinical trial patients participating in the clinical trial

1) An acute response (allergic, hypersensitive reaction) to Investigational Product

2) If the investigator determines that continuing participation is not appropriate due to the occurrence of a "serious adverse reaction".

3) In the event of a breach of the selection / exclusion criteria or a violation of a significant clinical study protocol.

4) Patients will be able to withdraw from the trial at their own request.

5) In case of no observation due to absence of clinical test patients.

6) If the other tester determines that the investigator should be stopped.

If the patient is withdrawn from the study, the Investigational Product should be discontinued and the date, reason, and findings should be recorded in the case record, along with all the results of the trial obtained to the point of withdrawal. If a clinical trial is excluded from clinical trials as a result of clinically significant laboratory performance, follow-up should be conducted until the event or laboratory performance is resolved or a reasonable period is determined.

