### Evaluation Method

#### 15.2.1 The primary efficacy end point

Compared to baseline (less than -4 weeks) before drug administration, test group vs. control group at 12 weeks after drug administration

Colposcopic biopsy was performed at visit 1 and visit 5 as a result of colposcopic biopsy, which is a Cervical intraepithelial neoplasia, after drug administration compared to baseline before drug administration. The test group and the control group are compared for the measured healing after 3 months compared with baseline

The stage of change in the Cervical intraepithelial neoplasia of this study is defined as follows.

- Regression: if healed in CIN I

→ Normal in CIN I

- Persistence: if CIN I step is the same without change

→ CIN I to CIN I

- Progression: In case of progressing more than 1 step in CIN I

→ CIN I, CIN II, CIN III, SCC (Squamous cell carcinoma).

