###### 15.3.2 Definition of analytical group

The analytical groups needed to assess efficacy and safety in this trial were performed in both the ITT and PP assay groups as defined below for efficacy assessments in accordance with national and international standards, Define the analysis and evaluate it as a reference.

Efficacy analysis group:

- Intent-to-Treatment (ITT) group: Defined as all subjects assigned to randomization after agreement to participate in the study. But patients who did not take the study drug at least once in the ITT group will be excluded from the analysis group.

- PP (Per Protocol) group: defined as the total subjects who completed the clinical study according to the study plan without any violation of the important research plan presented in 14.2 until the end of the study after the consent to participate in the study.

- In the efficacy evaluation, all the analyzes are performed in the ITT group and the PP group, and the final evaluation is decided according to the results of the ITT group analysis. If the results of the ITT group and the PP group are different, an additional analysis will be conducted exploring why the two analyzes are different.

Safety evaluation analysis group:

After agreeing to participate in the study, they will be defined as the whole subjects who were randomized and who took the research drug at least once.

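### LOCF scores every missing week-12 biopsy as not cured in the deciding ITT count, and conflicting exit rules let some of those biopsies go missing avoidably

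*Protocol*

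**What the plan says.** **Missing data.** Section 15.3.3: "LOCF (Last Observed Carried Forward) method is applied to replace missing values". This covers the efficacy variables. Safety variables are not imputed.

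**When the endpoint is measured.** Section 15.2.1: "Colposcopic biopsy was performed at visit 1 and visit 5". The schedule in 12.1 has no other biopsy and no early-withdrawal visit. The inclusion criteria require a CIN 1 diagnosis.

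**Who decides.** Section 15.3.2: "the final evaluation is decided according to the results of the ITT group analysis". ITT means randomised and dosed at least once. Section 15.3.4 decides on the difference between arms in the number of patients cured.

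**Passages that take patients out.** Under Prohibited drugs in section 11, when such a medicine is needed, "the clinical trial subject should stop the clinical trial". The list includes supplements, vitamins and Chinese medicine, and it applies throughout the trial period. That period runs to week 12, whereas dosing lasts 4 weeks. Section 14.1 names as a possible ground for dropout: "In the event of a breach of the selection / exclusion criteria or a violation of a significant clinical study protocol". On withdrawal it asks for the results obtained up to that point.

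**Passages that point the other way.** Concomitant medication investigation (section 12.2) disqualifies a patient only if the drug is expected to affect efficacy or safety. Section 14.2 treats interfering drugs and eligibility violations as exclusions from the PP analysis. Section 21.8 lets a patient with a serious violation continue if the sponsor approves.

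**The concern.** LOCF is normally a choice among several earlier observations. Here there is only one, and eligibility fixes its value. The method therefore amounts to scoring missing as not cured, although the protocol never says so.

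That convention is tolerable when missing biopsies are few and unavoidable. Here the exit rules can remove patients who still consent and could attend Visit 5, including patients whose dosing ended weeks earlier. Each one moves from a possible observed cure to a certain failure in an integer count judged against +2 and +11.

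Two things are at stake. Power falls even if both arms lose the same share. If the arms lose different shares, part of the difference in loss appears as a difference in cure.

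The sample size also does not match the analysis. Inflating 80 to 100 per arm assumes that dropouts leave the analysis, whereas ITT with LOCF keeps them in as failures.

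**Working it through.** **Inputs.** All come from section 9.3.1 unless stated.
- Design: "significance level : 0.05, statistical power : 80%, one-sided test".
- Control rate and effect: "we assumed that 31% of the cases of CIN 1 would resolve spontaneously, and a clinically significant difference was estimated at 20" percent. PGA row of the table: "1,500mg/day | 80 | 51% | 40.8". The same section also prints 81% against 51%, which does not fit its table. I used 51% against 31%.
- Stages of 43 and then 80 (43+37) per arm, with boundaries +2 and +11. Section 15.3.4 mixes more than 11 with less than 11. I used at least 11, because it reproduces the printed figures.
- Dropout 20%: 80 / (1 − 0.20) = 100 per arm.

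**Formula.** Let D1 and D2 be the PGA-minus-placebo differences in cures in the two stages. The trial is positive if D1 ≥ 2 and D1 + D2 ≥ 11. The probability is computed exactly from binomials with 43 and 37 per arm.

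**Reproducing the plan.** At 51% against 31%, power is 0.805 (printed 0.800). The type I error is highest at a cure rate of 50%, where it is 0.0461, and it is 0.035 at 31%. The printed 0.461 matches only as a misplaced decimal point for 0.0461.

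**Adding LOCF.** The carried value is always CIN I, so with loss d the counted cure rate is p × (1 − d). This assumes that, within an arm, loss is unrelated to whether the patient would have been cured. For example, with 20% loss in both arms, 0.51 × 0.80 = 0.408 and 0.31 × 0.80 = 0.248. The difference shrinks from 20 to 16 points, or from 16 to 12.8 patients in 80.

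**Results with 43+37 per arm, +2/+11, leavers included and scored uncured.** The splits between arms are assumptions. All have the protocol's 20% average loss, apart from the no-loss row.

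| Loss PGA / placebo | Power (51% v 31%) | False positive, 31% both arms | False positive, 50% both arms |
|---|---|---|---|
| 0 / 0 | 0.805 | 0.035 | 0.046 |
| 20 / 20% | 0.642 | 0.026 | 0.043 |
| 18 / 22% | 0.721 | 0.039 | 0.072 |
| 15 / 25% | 0.821 | 0.069 | 0.141 |
| 25 / 15% | 0.424 | 0.008 | 0.009 |

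The 15/25% row under no effect: 0.31 × 0.85 = 0.2635 against 0.31 × 0.75 = 0.2325, a spurious 3.1 points. The 25/15% row under the planned effect: 0.51 × 0.75 = 0.3825 against 0.2635, or 11.9 points. That is 9.5 patients in 80, below the boundary of 11.

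**At 100 per arm.** I assumed stages of 54+46 (43/0.8 and 37/0.8, rounded) and a final boundary of 12, which keeps the maximum type I error at 0.0495. Power is 0.884 with no loss and 0.744 with equal 20% loss. The inflation to 100 therefore does not restore 80% power under the analysis that decides the trial.

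**The case against.** **The exit rules are softer than one passage suggests.** A reader might infer that every patient who takes a prohibited medicine or breaches the protocol leaves without a week-12 biopsy. The documents do not say that. Section 14.1 lists grounds that can lead to dropout and limits them to eligibility breaches and significant violations. The concomitant-medication section is conditional, 14.2 removes violators only from PP, and 21.8 allows continuation. No passage forbids a biopsy after withdrawal. Its absence is inferred from the schedule and from recording results up to withdrawal. This objection stands. What remains is a conflict between passages that leaves the loss possible and avoidable.

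**Scoring missing as failure is a recognised convention and can be conservative.** This stands for equal loss: the false-positive rate is 0.026 at 31% and 0.043 at 50%, no higher than with no loss.

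**Unequal loss is not documented.** The trial is double-blind with matched bottles, dosing is short, and section 13.1 anticipates nothing beyond discomfort on taking the syrup. These make a large imbalance less likely without excluding it. The milder 18/22% split gives 0.039 at 31%, still below 0.05, and 0.072 at 50%.

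**Larger figures are tempting.** Keeping +11 at 100 per arm (54+46) gives 0.108 for a 15/25% loss at 31%. But that pairing already gives 0.051 at 31% and 0.065 at 50% with no loss, so part of the excess comes from the boundary. Section 15.3.4 also refers to a formula for differing final numbers, which is not shown, so +11 at 100 per arm cannot be taken as the planned rule.

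**Conclusion.** The point holds in this form. For the primary endpoint, LOCF is an unnamed missing-equals-not-cured rule inside the deciding ITT count. The protocol contradicts itself on whether patients who breach a rule stay to Visit 5, so some evaluable patients can become avoidable imputed failures.

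The firm cost is power. Under the protocol's own rule with equal 20% loss it falls from 0.805 to 0.642. At 100 per arm it falls from 0.884 to 0.744, on the assumed stage split and boundary.

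Bias depends on an imbalance that the documents do not predict. With 15/25% loss the false-positive rate is 0.069 at 31% cure and 0.141 at 50%. With 25/15% loss, power is 0.42. A reader might infer that LOCF inflates the type I error in general. It does so only if more placebo than PGA patients are lost, and by enough.

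This cannot simply be left to an analysis plan. The protocol fixes LOCF, the exit rules and the deciding population, and a biopsy never taken cannot be recovered.

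**What to change.** 1. Reconcile Prohibited drugs (section 11), Concomitant medication investigation (12.2), 14.1, 14.2 and 21.8. Whatever is decided about treatment, stopping treatment or breaching a rule should be stated and recorded separately from leaving follow-up.
2. State that patients who have not withdrawn consent attend the already scheduled Visit 5 biopsy, that ITT uses the result, and that PP still excludes them under 14.2.
3. In 15.3.3, replace LOCF for the primary endpoint with an explicit rule that a missing week-12 biopsy counts as not cured. This keeps the exact count rule in 15.3.4.
4. Add a tipping-point or multiple-imputation analysis as sensitivity only. Multiple imputation does not yield the integer difference that 15.3.4 tests, so making it primary would replace the decision rule.
5. In 9.3.1, state the power with dropouts counted as failures, since that is the analysis that decides.

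The cost is protocol wording, some effort to bring patients back to a visit already planned, and modest extra programming. ITT will then include outcomes observed after prohibited medication, which should be acknowledged when the result is interpreted.

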#### 15.3.4 Analysis of primary efficacy endpoints

In this study, the primary efficacy endpoint was to determine the cure rate as normal at the third month of drug administration of CIN I at baseline as described in 15.2.1 and compare the healing rates between the test and control groups.

The evaluation of the healing rate between the groups was based on the method proposed by Jung (2008). As described above, when 43 patients were selected in each group (intermediate analysis) in the first step, When the difference in number is less than 2 (test group-control group), it is judged that there is no effect of poly gamma glutamic acid, and the present study is terminated. If there were two or more difference in level 1, 37 patients were recruited in each group. In the case of more than 11 patients who were judged to be cured by 80 patients per group, it is judged that there is an effect of poly gamma glutamic acid. If it is less than 11, it is concluded that the effect of poly-gamma-glutamic acid is not ultimately.

If the final number of subjects is different in each analysis group after the end of step 2.

[figure not shown]

here,

n1, n2: Number of subjects per group in steps 1 and 2

a1, a: The first and final stages to determine whether to adopt the null hypothesis. The difference between the groups of healed subjects y1, y2, x1, x2:

b (y|n, p): probability distribution of binomial distribution

We will present the p-value based on the significance level formula.

In addition, the number of children, number of sex partners, and whether smokers are covariates during baseline diagnosis will be analyzed by logistic regression analysis using "exploratory analysis"

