| Statistical analysis | 1. General principles  Analyses will be descriptive in nature. Descriptive analyses will include the number of observations, mean, standard deviation, median, range, and interquartile range for continuous variables and the number and percent for categorical variables.  2. Populations  - ITT(Intent-to-Treatment): Defined as all assigned patients. However, patients who did not take the investigational product at least once in the ITT group should be excluded from the analysis group.  - PP(Per Protocol): PP analyses exclude all protocol major violation, including anyone who did not adhere to treatment, switched groups, or missed measurements.  - The final evaluation will be based on the results of the ITT group analysis.  3. Safety analysis  After agreeing to participate in the study, the study will be defined as the whole box of randomized, at least one investigational product.  4. Primary efficacy variable analyses  In the baseline, 3 months after the administration of CIN I, the patient was judged to be cured to normal, and the response rate between the PGA group and the control group was compared.  The evaluation of the healing rate between the groups is based on the method proposed by Jung (2008). When the results were confirmed by selecting 43 patients in each group, as in the previous step, the difference in the number of patients. In the case of less than 2 persons (PGA group-Control group), it was judged that there is no effect of PGA, and the present study is terminated. If there are more than 2 difference in level 1, 37 patients per group are recruited. In case of more than +11 patients who were judged as Histologic resolution by 80 patients per group, Histologic resolution of CIN. It is judged that there is an effect of PGA. If there is less than +11, it is concluded that the effect of PGA is not ultimately.  5. Secondary efficacy variable analyses  Secondary efficacy variable 1: Reid Colposcopic Index  0-2 Score: Likely to be CIN I  3-4 Score: Overlapping lesion - likely to be CIN I or CIN II  5-8 Score: Likely to be CIN II  The comparison between the baseline scores and the difference of the scores after 12 weeks will be confirmed through the t-test or the Wilcoxon rank sum test. In addition, considering the multinomial distribution of the grading system (0-2, 3-4, 5-8 points), the cumulative or ordinal logistic model of the changes in the grading system after 12 weeks compared to baseline.  Secondary efficacy variable 2: Pap Smear Test  The reading standard is based **on the 2001 Bethesda System for Reporting Cervical Cytologic Diagnoses**. The results of the study were divided into 6 stages: Negative, ASC-US, ASC-H, LSIL, HSIL, and Invasive cancer (Cervical carcinoma). Considering the multinomial distribution, And the cumulative or ordinal logistic model is used to analyze changes in the classification stage 3 months after the baseline.  Secondary efficacy variable 3: HPV DNA Chip Test  The HPV DNA Chip Test is a test to determine the type of virus infection. It is classified as positive or negative according to the test result. GEE (Generalized Estimating Equation) or Generalized Linear Mixed Model is considered to determine time-dependent changes, group-to-group differences, and time-to-group interactions for baseline versus measured clearance.  Secondary efficacy variable 4: HPV HC Ⅱ assay  GEE (Generalized Estimating Equation) or Generalized Linear Mixed Model is considered to determine time-dependent changes, group-to-group differences, and time-to-group interactions for baseline versus measured clearance.  Secondary efficacy variable 5: NK cell activity  To compare the results of NK cell activity measured at 4 weeks, 8 weeks, and 12 weeks versus baseline (0 week), the mean difference between the baseline and 12-week NK cell levels was calculated as t - Black or Wilcoxon rank sum test.  Secondary efficacy variable 6: MHC class II CD8, CD56 population  GEE (Generalized Estimating Equation) or Generalized Linear Mixed Model is considered to determine time-dependent changes, group-to-group differences, and time-to-group interactions for baseline versus measured clearance.  6. Safety analyses  All safety data, including all adverse events collected from patients, clinical laboratory test results, 12-lead ECG, and vital signs (blood pressure and pulse rate) are performed.  1) Adverse events  Summarize the adverse events observed following administration of the investigational product. The number of cases and the number of patients who experienced an adverse reaction, abnormal drug response, SAE, death, adverse events n that caused discontinuation of clinical trial, and / or "other significant adverse events (OAE) do. The number of patients who received each of the abnormal responses was also summarized by body-organ system (SOC), recommended language, and maximum severity for each treatment group. In addition to the summary statistics, the incidence or incidence of adverse events in the group are analyzed using Chi-squared test, Fisher's Exact test, or Poisson test.  2) Vital signs and laboratory tests  The results were analyzed by Chi-squared test, Fisher's Exact test, or Poisson test for each group of 12-lead ECG abnormalities at each time point. A summary statistic is presented and, if necessary, GLM or GLMM methods are used to perform group comparisons. |

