**[11] Study Methodology**

The purpose of this study was to investigate the effect of oral administration of poly-gamma glutamic acid (γ-PGA) on the Cervical Intraepithelial Neoplasia (CIN I) Double-blind, placebo-controlled study designed to identify immunomodulatory effects by assessing changes in immunological parameters.

In this study, a total of 80 patients (100 patients in the case of dropout) were participated in the study. Participation in the study was conducted in two stages as proposed by Jung (2008). In the first stage, 43 subjects were recruited in each group, and the main effect variable, healing, was checked. The difference in the number of subjects in the clinical trial for healing was less than 2 (the number of subjects who were treated for healing of poly-gamma glutamic acid - The number of subjects in clinical trials), it is judged that there is no effect of poly-gamma glutamic acid on cervical epithelial dysplasia and the study is terminated.

If there is more than one difference in step 1, we will consider a two-step study design that will enter step 2 and add an additional 37 patients per group. If the difference in the number of subjects in the clinical trial between group 1 and group 2 of 80 patients in each group is greater than 11 patients, the effect of γ-PGA will be confirmed. Otherwise, γ-PGA. It will be judged that it is not effective in healing the injured Cervical Intraepithelial Neoplasia (CIN I).

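### The two-stage decision rule is worded differently in three places, leaves boundary results undecided, and as written in Section 11 gives 76% power, not the stated 80%

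*Protocol*

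**What the plan says.** Write D1 for the PGA-minus-placebo difference in cured patients at 43 per group, and D for the same difference at 80 per group. The design table in Section 9.3.1, repeated in the Protocol Outline, gives boundaries of +2 and +11, a power of 0.800 and a significance level printed as 0.461. The stated targets are "significance level : 0.05, statistical power : 80%, one-sided test".

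The rule itself is then written out three times.

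- **Protocol Outline, Statistical analysis, item 4.** Stop if D1 is below 2. "If there are more than 2 difference in level 1, 37 patients per group are recruited". At the end, more than +11 is an effect and less than +11 is no effect.
- **Section 11, Study Methodology.** Stop if D1 is below 2. "If there is more than one difference in step 1, we will consider a two-step study design". At the end, if the difference "of 80 patients in each group is greater than 11 patients, the effect of γ-PGA will be confirmed", and any other result counts as not effective.
- **Section 15.3.4.** Stop if D1 is below 2. "If there were two or more difference in level 1, 37 patients were recruited in each group". At the end, more than 11 is an effect. "If it is less than 11, it is concluded that the effect of poly-gamma-glutamic acid is not ultimately".

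**The concern.** The statistic is a whole number, so the rule must say what happens at each boundary value. The three texts do not agree on D1 = 2 or on D = 11, and two of them give no outcome for D = 11 at all. None of the three, as prose, makes +11 a success, although the design table appears to have been computed that way.

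This is the primary analysis and the basis for declaring an effect. A gap at the boundary would have to be closed once the count is known, which is when the choice is no longer neutral. At stage 1 the gap decides whether 74 more patients (37 per group) are recruited. If Section 11 is followed to the letter, the trial is also less powerful than the protocol claims.

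**Working it through.** **Inputs, all from Section 9.3.1 and Section 11**

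- Stage sizes: 43 per group, then 37 more, 80 in total.
- Control rate and difference: "we assumed that 31% of the cases of CIN 1 would resolve spontaneously, and a clinically significant difference was estimated at 20" percentage points, so 31% against 51%. The sample-size table also lists 51% for PGA.
- One-sided level 0.05, target power 80%.

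**Formula**

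At each stage the difference of two independent binomial counts has

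P(D = d) = Σ_y b(y + d | n, p_PGA) · b(y | n, p_placebo).

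With D2 the difference among the second-stage patients (37 per group), the probability of declaring an effect is

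Σ over d ≥ a1 of P(D1 = d) · P(D2 ≥ a − d),

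where a1 is the smallest D1 that continues and a is the smallest D that succeeds. Power is taken at 51% versus 31%. Alpha is the maximum over a common response rate, reached near 0.50.

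**Reproducing the plan's own figures first**

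With a1 = 2 and a = 11, power is 0.8049 and maximum alpha is 0.0461. The table prints 0.800 and 0.461. The power agrees, and the digits of alpha agree if the decimal point was misplaced.

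**The other readings**

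| Continue if | Effect if | Power | Maximum alpha | Where it comes from |
| --- | --- | --- | --- | --- |
| D1 ≥ 2 | D ≥ 11 | 0.805 | 0.0461 | matches the design table |
| D1 ≥ 2 | D ≥ 12 | 0.762 | 0.033 | Section 11; also 15.3.4 if 11 is not a success |
| D1 ≥ 3 | D ≥ 11 | 0.793 | 0.044 | Outline's stage 1 wording with the table's +11 |
| D1 ≥ 3 | D ≥ 12 | 0.753 | 0.032 | Outline, if only what it names as continue and success counts |

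**How likely the boundary results are**

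- Reaching stage 2 and finishing at exactly +11 under 51% versus 31%: 0.8049 − 0.7620 = 0.0429, about 4.3%.
- Exactly +2 at stage 1 is the rise in the probability of early stopping when the cut-off moves from D1 < 2 to D1 < 3. Under 51% versus 31% it is 0.087 − 0.057 = 0.030. Under a common rate of 31% it is 0.720 − 0.637 = 0.083.

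**The boundary values side by side**

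| Result | Outline | Section 11 | Section 15.3.4 |
| --- | --- | --- | --- |
| D1 = 2 | no outcome | continue | continue |
| D = 11 | no outcome | not effective | no outcome |

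**The case against.** The best defence is that the intended rule can be recovered. All three texts stop below 2, Sections 11 and 15.3.4 agree on continuing at 2, and no text stops the trial at 2. The stage 1 problem is therefore a gap in the Outline, not a head-on contradiction. That is fair, and the two rows with D1 ≥ 3 show what happens only if the Outline is read strictly.

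Second, Section 15.3.1 calls for a one-sided 5% test, and Section 15.3.4 promises a p-value from the significance-level formula. At 80 per group, +11 has a maximum level of 0.046, so that test would call it an effect. But 15.3.4 introduces the p-value for final numbers that differ, and at 80 per group it would contradict Section 11. This is a further inconsistency and does not resolve the first. The formula is not visible in the text at hand, so its inequalities may state the inclusive pair; the claim here is limited to the prose.

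Third, success above 11 is also the wording in the Outline and 15.3.4, so the lower power is not peculiar to Section 11. That stands. Section 11 differs in that it expressly makes 11 a failure.

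Fourth, power alone does not identify the inclusive pair, since 0.793 is nearly as close to 0.800 as 0.805 is. That also stands. The identification rests on alpha, 0.0461 against 0.0442, and on reading the printed 0.461 as a decimal slip. A one-sided level of 0.461 cannot be meant beside a stated 0.05.

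Last, Section 9.3.1 also has a line with 81% versus 51%. Power there would be 0.989 or 0.984 under the first two rules in the table of readings. Those rates do not fit the design, because a single-stage calculation would need only 30 per group.

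**Conclusion.** The point holds. The primary decision rule is stated inconsistently, a final difference of exactly 11 is a failure in one section and undecided in two, and a stage 1 difference of exactly 2 is undecided in the Outline. The stated 80% power belongs to the inclusive rule (0.805). Under Section 11's wording it is 0.762, a loss of about 4 percentage points, with alpha falling from 0.046 to 0.033. Every reading keeps alpha below 0.05, so the harm is to power and to an unambiguous decision, not to the type I error rate. The figures assume 51% versus 31%, exactly 43 and then 80 evaluable patients per group, and that the printed 0.461 stands for 0.0461. Because this is the rule that decides the trial, it must be corrected.

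**What to change.** Put one rule, in the same words, into the Protocol Outline, Section 11 and Section 15.3.4:

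- Stage 1, 43 per group: stop if D1 ≤ 1, continue if D1 ≥ 2.
- Final, 80 per group: declare an effect if D ≥ 11, no effect if D ≤ 10.

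Beside it, state the operating characteristics: maximum one-sided alpha 0.046 and power 0.805 at 51% versus 31%. Correct the printed 0.461 in both copies of the design table at the same time. Check that the inequalities in the 15.3.4 formula agree with this rule. The cost is an amendment to wording, with no extra patients and no change to the design.
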